### Outcomes

Assessments pre- and post the intervention or control period will be conducted by the same blinded assessor (physiotherapist). Demographic data (age, gender, height, weight,) including information specific to history of Polio and mobility will be gathered at the baseline assessment. A combination of self-report questionnaires and objective measurements will be used at baseline and follow-up. An exit questionnaire, requesting feedback on participant’s experiences will be provided at the end of the participation period.

The primary outcome measure will be a change in physical fitness measured using the Six-Minute Arm Test (6-MAT)
[29]. This is a submaximal exercise test conducted using upper limb ergometry. Heart rate and rate of perceived exertion using the BORG 6–20 scale (RPE) are recorded during six minutes of arm cycling at a predetermined power output, based on physical ability. This test was developed for patients with spinal cord injury and has acceptable test-retest reliability and validity. Power output levels were adapted from those defined for spinal cord injury patients to suit the profile of Polio survivors.

The secondary outcome measures will be changes in

(i) Self reported physical activity, assessed using The Physical Activity Scale for People with Physical Disabilities questionnaire
[30,31]. Validity of this questionnaire has been examined and found acceptable in a group of patients with disability, including Polio survivors.

(ii) Body composition, assessed using Body Mass Index and waist to hip ratio as described by ACSM
[32].

(iii) Energy cost of walking, using the Physiological Cost Index (PCI). The PCI was developed by MacGregor and combines assessment of heart rate and walking speed
[33]. There are varying reports of validity and reliability in different patient groups, for example it is valid and reproducible (ICC=0.89) in children with cerebral palsy, although less sensitive than direct measurement of oxygen cost
[34]. The PCI is a clinically accessible proxy measure of energy cost, not requiring expensive equipment. It was previously successfully used in a similar group of Polio survivors
[35].

(iv) Fatigue measured using the Fatigue Severity Scale (FSS)
[36,37]. The FSS is reported as being applicable to Polio survivors with a better ability to distinguish those with disabling fatigue from those without
[37]. Reproducibility of the FSS in Polio survivors is good (ICC 0.83)
[38].

(v) Quality of Life using the SF-36v2
[39,40] . The SF-36 is a measure of health status and quality of life, and has been used in several studies in Polio survivors
[39-41].

(vi) Pain, assessed using the Short Form McGill Pain questionnaire version 2
[42], body diagrams to document pain location and visual analogue scales. Visual analogue scales and body diagrams have been used in several studies of Polio survivors
[20,43-45].

(vii) Upper limb strength (maximum voluntary isometric contraction, KGs), measured using fixed dynamometry using the Quantitative Muscle Analysis (QMA) system
[46]. Shoulder abduction, adduction, elbow flexion and extension and hand grip will be measured using strictly standardised methods previously described
[46-48]. Each test is completed if the participant has adequate power to generate a resistance against the load cell or dynamometer. If not a score of zero is given.

(viii) Hand grip motor fatigue**,** measured using QMA
[48].

### Statistical analysis

Data will be coded and collated in a Microsoft Excel® spreadsheet and Stata 12 will be used for statistical analysis. All analyses will be conducted on an intention-to-treat principle
[49]. Missing data will be managed using the last observation carried forward method. Per-protocol analyses will be performed excluding participants with major deviations from the treatment protocol (defined as less than 50% compliance with treatment). Demographic characteristics and baseline data will be summarised using descriptive statistics and baseline comparability of the groups will be examined. The distribution of the data will be assessed and if appropriate, parametric methods will be used in analysis. Two sample t-tests will be used to compare groups and paired t-tests will be used for within group comparisons. The non-parametric equivalent will be used where data are not normally distributed. A significance level of p<0.05 will be set. The primary analysis will examine the difference between intervention and control groups. A secondary analysis will compare pre and post intervention scores and will include control participants who crossed over to the intervention group.

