## Methods

### Study design

This is a prospective, single blinded, randomised controlled trial. There are two arms (i) exercise intervention using arm ergometers and (ii) control. It will not be possible to blind the treating physiotherapist or the patient to the exercise intervention; hence the single (assessor) blinded design. The protocol was approved by the Beaumont Hospital Medical Research ethics committee in November 2009. The trial was designed incorporating recommendations of the CONSORT statement
[24]. The flow of participants through the study is represented in Figure 
1. All participants will receive usual Physiotherapy care, which does not routinely include arm ergometry. Participants in the control group can choose to cross over to the exercise intervention arm after the eight week control period. Assessments will be completed at baseline and at eight weeks.

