### Sample size

The sample size for the study was determined based on a hypothesised change in heart rate of eight beats per minute, during the six minute arm test. Change in fatigue was also examined. The change in heart rate was based on reported changes in previous exercise interventions and considered clinically significant
[17,25]. For each calculation power was set at 80%, alpha at 5% and drop-out rate at 15%. The formula N= 2 [(standard deviation)^2^/(difference)^2^ x 7.9 was used. We aim to recruit 120 participants (60 per group). Table 
2 outlines the number of participants required based on the six minute arm test and the fatigue severity scale.

**Table 2 T2:** Sample size calculation

**Outcome measure**	**Clinically significant difference**	**Standard deviation**	**Number of participants required per group**
6MAT (Heart Rate)	8 b/m	14.5	60
FSS	1 point	1.1	48

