Participants will monitor fatigue and pain on 0–10 Visual Analogue Scales. If there is an increase of more than 2 points in upper limb, neck or back pain, or subjective fatigue, the participant will be advised to reduce exercise duration and/or intensity. If this does not result in an improvement, the participant will be advised to contact the treating physiotherapist by phone. This physiotherapist will then make a decision on how to proceed and the participant will be managed appropriately and withdrawn from the study if necessary. All adverse events will be recorded and managed according to a detailed policy. Participants randomised to the control group will be advised to continue with normal activities and will receive physiotherapy care as appropriate.

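### With assessments only at baseline and eight weeks, last observation carried forward enters every missing outcome as an observed zero change, which is unbiased in general only if leavers truly did not change

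*Protocol article*

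**What the plan says.** All statements are in the protocol article.

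- Statistical analysis fixes the missing-data rule: "Missing data will be managed using the last observation carried forward method". It also says "All analyses will be conducted on an intention-to-treat principle" and "Two sample t-tests will be used to compare groups and paired t-tests will be used for within group comparisons". It names no other method for missing data.
- Study design sets the schedule: "Assessments will be completed at baseline and at eight weeks". Outcomes confirms one assessment before and one after the intervention or control period. The primary outcome is change in fitness on the Six-Minute Arm Test (6-MAT). Fatigue, pain and upper limb strength are secondary.
- Sample size rests on a "hypothesised change in heart rate of eight beats per minute, during the six minute arm test", SD 14.5, 80% power, 5% alpha and 15% drop-out, giving 60 per group. It does not say whether 14.5 is the SD of the change or of the score.
- Intervention describes what happens if an exerciser's pain or fatigue rises and does not settle after exercise is reduced: the physiotherapist decides how to proceed, and "the participant will be managed appropriately and withdrawn from the study if necessary". Adverse events are recorded under a separate policy.
- The Background hypothesis includes no increase in pain or fatigue, and the Discussion promises safety information on pain, fatigue and muscle strength.

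**The concern.** Carrying the last observation forward is usually discussed for trials with several follow-up visits. Here there is one. The only observation before a missing eight-week value is the pre-randomisation value, so the rule is baseline carried forward. It records a change of exactly zero and treats it as data.

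Two things are at stake. The first is the primary effect estimate and its interval, because the plan itself expects about 9 of 60 participants per arm to be lost. The second is the comparison of pain, fatigue and strength. The protocol describes a route by which an exerciser could leave because pain or fatigue got worse. Such a person, if not assessed at eight weeks, would enter the analysis as unchanged on the very scales meant to show that worsening.

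**Working it through.** **Plan's own figure.** 2 × (14.5² / 8²) × 7.9 = 51.9, so 52 per group. 52 × 1.15 = 59.8, so 60 per group, as stated (52 / 0.85 would give 62).

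**Inputs.** From Sample size: effect 8, SD 14.5, n = 60 per arm, drop-out 15%. Assumed: 14.5 is the SD of change; controls do not change on average; drop-out is unrelated to outcome. Benefit is counted as positive.

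**General bias.** Let p1 and p0 be the drop-out proportions (exercise, control), and m1 and m0 the leavers' true mean changes. The rule replaces m1 and m0 by 0, so

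bias = −(p1 × m1 − p0 × m0).

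This vanishes if leavers did not change, or if the two terms happen to cancel.

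**Base case, 15% in each arm.**
- Estimate: 0.85 × 8 = 6.8.
- Exercise-arm variance: 0.85 × 14.5² + 0.15 × 0.85 × 8² = 178.71 + 8.16 = 186.87. Control-arm variance: 178.71.
- SE: √((186.87 + 178.71) / 60) = 2.47.
- Power: Φ(6.8 / 2.468 − 1.96) = 78.7%.
- Completers only, 51 per arm: SE = 14.5 × √(2/51) = 2.87; power Φ(8 / 2.871 − 1.96) = 79.6%.
- Coverage of 8.0: the centre is off by 1.2 / 2.468 = 0.486 SE, so coverage is Φ(1.96 + 0.486) − Φ(−1.96 + 0.486) ≈ 92%. Simulation agrees (about 92%).

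**Unequal drop-out (assumed; no document gives arm-specific rates).** Same formulas, exercise/control, true effect 8:

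| Drop-out | Common change in both arms | Estimate | Power | Completers' power |
|---|---|---|---|---|
| 20%/10% | 0 | 6.4 | 73% | 79% |
| 25%/5% | 0 | 6.0 | 68% | 79% |
| 10%/20% | 0 | 7.2 | 83% | 79% |
| 5%/25% | 3 beats | 0.95 × 11 − 0.75 × 3 = 8.2 | 91% | 79% |

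**No true effect (assumed).** With 25%/5% drop-out and a 5-beat change common to both arms, the expected difference is 0.75 × 5 − 0.95 × 5 = −1.0 beat. With SE 2.46, type I error is about 6.9%.

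**If 14.5 is the SD of the score.** Take 14.5 at both visits and compare eight-week scores at 15%/15%. The estimate is still 6.8. SE = √((14.5² + 8.16 + 14.5²) / 60) = 2.67. Power is Φ(6.8 / 2.673 − 1.96) = 72% against 79.6% for completers, and coverage of 8.0 is about 93%. The near-equality of power therefore depends on reading 14.5 as the SD of change.

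**Harm outcomes (assumed illustration).** If 9 of 60 exercisers leave having worsened by 3 points on a 0–10 pain or fatigue scale, they should add 9 × 3 / 60 = 0.45 points to the arm mean. Under the rule they add 0.

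**The case against.** Four objections deserve an answer.

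- **The standard error.** A reader might infer from 2.47 against 2.87 that the reported standard error is 14% too small. It is not. These belong to two different estimators. In simulation of the base case the reported SE averages 2.46 and the estimator's actual sampling SD is 2.47; the interval covers the rule's own target, 6.8, about 95% of the time. It is smaller mainly because the estimate is scaled by about 0.85. The loss of coverage for 8.0 comes from the shifted centre alone. This objection stands in full.
- **The direction.** A reader might infer that the effect is always pulled towards zero. The figure of 6.8 is biased only if leavers would still have gained the full 8 beats. If they stop exercising, gain nothing, and controls are stable, the as-randomised effect is 0.85 × 8 = 6.8, the rule is unbiased, and the completers' 8.0 is too high. This also stands. It does not rescue the rule, which assumes that answer for everyone instead of examining it.
- **Informative drop-out.** The protocol makes withdrawal after persistent pain or fatigue possible for exercisers, as a last step. It does not say this will be common, that drop-out will differ by arm, or that a withdrawn participant misses the eight-week assessment; participants in either arm may withdraw at any time. Informative drop-out is a risk, not an established fact.
- **Hidden harm.** A reader might infer that harm disappears from view. Adverse events are recorded separately, and exercisers monitor pain and fatigue themselves. What can be masked is worsening in the scored between-group comparison.

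Two other defences fail. The planned per-protocol analysis excludes on compliance below 50% and does not deal with missing values. Nor can the choice be left to an unseen analysis plan, because the article commits to the method.

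**Conclusion.** The point holds and should be fixed. Under this schedule the stated rule is baseline carried forward, and nothing else in the document repairs it.

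On the plan's own figures, with 14.5 as the SD of change, stable controls and drop-out unrelated to outcome, the expected estimate is 6.8 instead of 8.0 and the 95% interval covers 8.0 about 92% of the time. The damage there is to the estimate and its interval; the test is nearly unaffected. Larger effects on power or type I error need assumed unequal drop-out, and the false difference also needs an assumed common change. The error can go either way.

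For pain, fatigue and strength, the rule leans towards a finding of no worsening if exercisers leave because they are worse and are not assessed. The document makes that possible but gives no rate, so its size cannot be stated.

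**What to change.** - **Primary analysis.** Replace the last-observation sentence with a likelihood-based or multiple-imputation analysis of the eight-week value under missing-at-random, with baseline value, gender (the stratification factor) and arm in the model, and participants analysed as randomised. With a single follow-up, the likelihood version amounts to covariance analysis of those observed, so precision will honestly reflect about 51 per arm.
- **Sensitivity analysis.** Missing-at-random does not by itself cover drop-out driven by worsening. For pain, fatigue and strength, add an analysis in which exercise-arm drop-outs are assumed worse by a stated delta, over a range fixed in advance.
- **Data collection.** State that participants who stop the exercise are still invited to the eight-week assessment. This concerns data collection only and leaves the decision to stop exercise as it is.

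The cost is a change of wording, a little more analysis work and a wider interval. No extra participants or visits are needed.

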### Randomisation

The randomisation sequence will be created prior to study commencement using
http://www.randomization.com. A 1:1 allocation in block sizes of 10 and stratified by gender will be used. Group allocation will be concealed from the blinded assessor using sequentially numbered sealed opaque envelopes, colour coded by gender. Envelopes will be opened with the participant by the treating physiotherapist, after baseline assessments have been completed. Gender stratification is necessary to avoid weighting of sexes to any particular group, which may skew physical fitness data.

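### The between-group t-test uses baseline only by subtraction and leaves out gender, the stratification factor; it is valid, but ANCOVA would be more precise at no cost

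*Protocol article*

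**What the plan says.** The Statistical analysis section fixes the test: "Two sample t-tests will be used to compare groups", with paired t-tests inside each group. For skewed data, "The non-parametric equivalent will be used where data are not normally distributed". It names no baseline covariate and no gender term. It says that baseline comparability will be examined, but attaches no consequence to the result.

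The data for an adjusted analysis are collected. Under Study design, "Assessments will be completed at baseline and at eight weeks". Under Outcomes, "The primary outcome measure will be a change in physical fitness measured using the Six-Minute Arm Test (6-MAT", and the secondary outcomes are likewise introduced as changes. The Statistical analysis section does not itself say whether the t-test is applied to change scores or to 8-week values; the Outcomes section points to change.

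Under Randomisation, "A 1:1 allocation in block sizes of 10 and stratified by gender will be used", and the reason is given: "Gender stratification is necessary to avoid weighting of sexes to any particular group, which may skew physical fitness data".

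**The concern.** The design treats gender as important enough to stratify on, and measures each outcome before treatment. The analysis then uses baseline only as something to subtract, and does not use gender. Three things follow.

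- **Efficiency.** Subtracting baseline gives it a fixed coefficient of 1. When the baseline/8-week correlation is below 1, that coefficient is too large and the change score carries avoidable noise.
- **Chance imbalance.** A change score is negatively correlated with baseline. If the arms happen to differ at baseline, part of that difference passes into the estimate through regression to the mean. The plan looks at comparability but does not say what follows from it.
- **Stratification.** If gender predicts the analysed outcome, stratifying on it reduces the true variability of the treatment difference. An unadjusted standard error does not reflect this and is too large.

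The margin is thin: the sample size aims for 80% power with no reserve.

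**Working it through.** **Inputs from the Sample size section:** difference 8 beats per minute, SD 14.5, power 80%, alpha 5%, drop-out 15%, 60 per group. The multiplier 7.9 is close to (1.96 + 0.84)² = 7.84, so the test is taken as two-sided. The section does not say whether 14.5 is the SD of change or of a single heart rate.

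**The plan's own figure.** 2 × (14.5² / 8²) × 7.9 = 51.9, so 52 per group; 52 × 1.15 = 59.8, so 60. The stated 60 reproduces.

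**Planned test.** Evaluable per arm: 60 × 0.85 = 51. Standard error: 14.5 × √(2/51) = 2.87. Noncentrality: 8 / 2.87 = 2.79. The noncentral t distribution gives 78.8% power.

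**ANCOVA.** Let r be the correlation between baseline and 8-week value, with equal variance σ² at both visits. The change score has variance 2σ²(1 − r) and the ANCOVA residual has variance σ²(1 − r²). Their ratio is (1 − r²) / [2(1 − r)] = (1 + r)/2, which is below 1 for every r below 1. The ANCOVA variance is also below the 8-week variance σ² whenever r is not zero. So for 0 < r < 1 ANCOVA beats both t-tests; only the size of the gain depends on r, which the document does not give.

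If 14.5 is the SD of change, the ANCOVA residual SD is 14.5 × √((1 + r)/2):

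| r (assumed) | residual SD | ANCOVA power | t-test on change |
|---|---|---|---|
| 0.3 | 11.69 | 92.8% | 78.8% |
| 0.5 | 12.56 | 89.0% | 78.8% |
| 0.7 | 13.37 | 84.9% | 78.8% |
| 0.8 | 13.76 | 82.9% | 78.8% |
| 0.9 | 14.13 | 80.8% | 78.8% |

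If 14.5 is instead the SD of a single heart rate, the change score has SD 14.5 × √(2(1 − r)) and the ANCOVA residual 14.5 × √(1 − r²). Power on change versus ANCOVA is then 64.5% vs 82.4% (r = 0.3), 78.8% vs 89.0% (0.5), 94.5% vs 97.2% (0.7) and 99.2% vs 99.6% (0.8).

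**Chance imbalance.** With a single-measurement SD of 14.5 and 60 per arm, the baseline difference has standard error 14.5 × √(2/60) = 2.65. An imbalance of one standard error shifts the change-score estimate by (1 − r) × 2.65: about 1.3 beats per minute at r = 0.5 and 0.8 at r = 0.7, against a target of 8.

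**Gender.** The document gives no figure for how much variance gender explains, so its contribution cannot be computed. If gender shifts heart rate equally at both visits, the shift cancels in the change score.

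**The case against.** A reader might infer that the plan ignores baseline altogether. The Outcomes section does not support that: outcomes are changes, so a two-sample t-test on them uses baseline by subtraction. Only an analysis of the 8-week value alone would ignore it, and that reading fits the Outcomes section poorly.

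A reader might also infer that the test is biased or invalid. It is neither. Under 1:1 randomisation the t-test on change is unbiased. A chance imbalance affects the one trial that is run, not the expectation over trials, and leaving out a prognostic stratification factor makes the test conservative rather than liberal.

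The gain can also be small. The Outcomes section calls the 6-MAT's test-retest reliability acceptable and gives an ICC of 0.83 for the Fatigue Severity Scale, so a high r is at least as plausible as a low one. At r = 0.8 to 0.9 the gain is 2 to 4 points if 14.5 is the SD of change. The largest gap, 64.5% to 82.4%, needs both r = 0.3 and the single-measurement reading of the SD, and the document establishes neither. The gain from gender may be close to nil for change scores. The 6-MAT power output is also set by physical ability, which may weaken any link between gender and test heart rate.

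Finally, this is a condensed article, and supporting adjusted analyses may be described elsewhere. That argument does not cover the main test: the article names it, so the choice is open to comment.

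These points limit the size of the concern and rule out any claim of invalidity. They do not reverse the direction, since ANCOVA has the smaller variance throughout 0 < r < 1.

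**Conclusion.** The point holds as one of efficiency and of protection against chance imbalance. The plan fixes an unadjusted test, uses baseline only by subtraction, and leaves out the factor on which it stratified. Taking 14.5 as the SD of change, ANCOVA would raise power from 78.8% by about 14 points at r = 0.3, 10 at 0.5, 6 at 0.7, 4 at 0.8 and 2 at 0.9.

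This rests on 51 evaluable participants per arm, a two-sided 5% test, equal variances at the two visits and an assumed r. No size can be put on the gender term. The change is worth making because it is free and the planned power has no reserve, not because the stated analysis would mislead.

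**What to change.** In the Statistical analysis section, state that the primary comparison is an ANCOVA of the 8-week 6-MAT heart rate on arm, baseline 6-MAT heart rate and gender, reported as the adjusted difference with its 95% CI. This also settles whether change or the 8-week value is analysed, because the treatment coefficient is the same for both once baseline is in the model.

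Use the same model for continuous secondary outcomes where its assumptions are reasonable. Check this in particular for strength, where participants unable to perform a test score zero. Keep the two-sample t-test, or its non-parametric equivalent, as a sensitivity analysis.

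The cost is a sentence or two of text. Baseline values and gender are already collected, and the sample size need not change.
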